### Participant retention

In accordance with the Danish National Scientific Ethics Committee’s guidelines for remuneration or other benefits to voluntary participants, all healthy participants (sub-study 1) will receive remuneration corresponding to their time participating in neuropsychological examinations, neuroimaging, and treatment sessions. Patients (sub-study 2) will be offered feedback on the results of their neuropsychological assessments after completing the final assessment. In accordance with the Danish National Scientific Ethics Committee’s guidelines for remuneration or other benefits for patient participants, they will receive gift cards for neuropsychological examinations and neuroimaging. In addition, all participants in both studies will receive transport allowance in connection with the various study days.

## Discussion

Cognitive impairment across domains is highly prevalent in several neuropsychiatric disorders, which impedes recovery and psychosocial functioning. A key challenge that hampers discovery of cognition treatments with robust and long-lasting efficacy is the incomplete insight into the mechanisms underlying long-lasting neuroplasticity. Emerging evidence suggests cognitive benefits of moderate hypoxia training in humans and animal studies [76], possibly through increased EPO expression triggered by hypoxia [36]. Nevertheless, there are no well-controlled studies with multiple outcomes that also includes mechanistic translational work. The objective of the present trial is therefore to investigate the effects of a three-week hypoxia (12% O_2_) cognition training intervention in healthy individuals (sub-study 1) and remitted patients with affective disorders (sub-study 2) on cognition, daily functioning, and brain function and neuroplasticity. The results will provide insights into potential pro-cognitive effects of hypoxia cognition training and may influence future treatment strategies targeting cognition and neuroplasticity across brain disorders.

### Strengths

The present trial involves a multidisciplinary research approach that capitalizes on the relative strengths of each approach. In basic scientific studies in healthy humans (sub-study 1), we will elucidate the causal mechanisms of changes in neuroplasticity and cognition across multiple levels of scientific analysis from presynaptic density measured with PET and neurocircuitry network activity measured with fMRI to neurocognitive tests. Furthermore, the clinical study (sub-study 2) will clarify whether targeting these mechanisms translates into cognitive and functional benefits in cognitively impaired patients with mood disorders. With the four treatment arms in the basic scientific study (sub-study 1), we will be able to determine the combined—potential synergistic—effects of hypoxia and cognitive training and the separate effects of these treatment modalities. The trial also complies with the expert recommendations by the ISBD Cognition Task Force to select a broad cognitive composite score spanning attention, memory, and executive function as *primary outcome* in cognition trials in mood disorders [54]. Furthermore, the inclusion of self-reported, observer-rated, and performance-based measures of functioning will provide insight into whether potential cognitive benefits of EPO translate into improved daily functioning, which is the ultimate goal for our patients. Finally, the use of neuroimaging and blood-based measures will provide mechanistic insights into potential cognitive improvement induced by hypoxia cognition training, in line with international recommendations [61].

### Limitations

The extensive somatic illness exclusion criteria limits generalizability of findings. However, these exclusion criteria are necessary to ensure participant safety of this novel repeated hypoxia training intervention, which is of principal importance. In particular, a large proportion of patients with mood disorders have somatic comorbidities. Therefore, if the present trial reveals positive effects on cognition, important next steps would be to examine the safety of hypoxia training in patients with somatic comorbidities. Furthermore, the included patients with BD and MDD are mostly on psychotropic medication. While this supports generalizability of the findings, since we want to target residual cognitive impairments in symptomatically stable patients who are mostly medicated, these concomitant medications may also confound [54] cognitive test, PET, and fMRI results [77]. To minimize confounding effects, patients’ medication will be kept stable during the study participation period, if possible, and by accounting for medication status in post hoc analyses. In addition, since the healthy group is primarily recruited from University of Copenhagen, it is possible that they have less capacity than patients for cognitive and synaptic changes. Finally, it is a potential limitation that we based our power calculations on the effect size demonstrated in a study of EPO treatment rather than a hypoxia study, which may be more directly comparable. However, the expected change of 0.4 SD in cognition corresponds to a clinically relevant cognitive enhancement as defined by the ISBD task force [7].

### Study feasibility

While our recent mouse studies [36, 38] provide a firm basis for ALTIBRAIN, and our longstanding work on EPO treatment of cognitive impairment across animals and humans lends significant support, the translation of findings from animals to humans is often poor [11]. There is therefore a risk that we find no substantial cognitive improvements in humans. In this case, our multidisciplinary approach Notwithstanding the risk, we evaluate the chances of detecting treatment-related cognitive improvements in humans as high based on our previous findings that pro-cognitive effects of EPO treatment seemed to translate from rodents to humans [25–28, 30–33, 78–80] and were accompanied by brain changes as assessed with functional and structural MRI across healthy human participants [26, 27] and patients with neuropsychiatric disorders [24, 28, 31, 34] and that similar functional neuronal changes were observed with intensive cognitive training [81].

### Safety procedures and monitoring of hypoxia training

The procedure involves repeated exposure to normobaric 12% O_2_, which corresponds to an altitude of 4400 m. Similar daily repeated exposures to simulated altitudes of 4–8000 m over days to weeks are used widely, including by the US army, to induce high-altitude acclimatization and minimize risk of altitude sickness upon subsequent ascend to high altitudes [82]. We therefore evaluate the risk of altitude sickness in our study as minimal. Nevertheless, as safety precautions, we will (i) apply a 30-min lead-in phase, where oxygen levels are reduced slowly from 16 to 12% to allow for physiological adjustment; (ii) exclude individuals with risk factors for altitude sickness; (iii) monitor potential symptoms of altitude sickness at a daily basis with the Environmental Symptoms Questionnaire (ESQ) related to cerebral function [83]; and (iv) collaborate with medical doctors at the Frederiksberg Hospital ([name], [name], [name]) as in our previous EPO intervention studies. We will report the mean ESQ scores in the primary outcome articles in addition to any adverse events that may occur during the intervention.

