### Randomization and blinding

Randomization is conducted in the database program REDCap [51], which is also used to store the collected data, utilizing a 1:1 allocation ratio. Randomization occurs after inclusion of the participants planned to undergo treatment sessions together. Treatment groups are stratified for age (> 27 in sub-study 1 of generally young volunteers/ > 35 in sub-study 2 of patients). For randomization purposes, date of birth is registered to determine the stratum to which the participant belongs at the time of enrolment. Study identification numbers are given consecutively within each stratum and treatment arm. Randomization is conducted in the randomization module in REDCap, where an un-blinded researcher inputs the stratum and the program then retrieves the allocated intervention. To ensure blinding of the outcome-assessors, the randomization module in REDCap is only accessible to the researchers, who are not involved in evaluation of the efficacy parameters.

Healthy participants in sub-study 1 are blind to the oxygen condition since the low/normal oxygen air blown into the room is of equal temperature and humidity. Furthermore, they are told that they receive one of two forms of cognitive training, which effectively blinded participants in a previous study [52]. After study completion, we will assess whether blinding has been maintained for each participant, since there is a small risk that some participants develop symptoms of mild altitude sickness which could unblind them to their intervention. Blinding of the outcome assessors is ensured by their absence during the training visits (where oxygen levels are displayed and monitored on a screen outside the room). Participants will be instructed not to disclose any information concerning their intervention during outcome assessments and under no circumstances will the allocation be revealed to the outcome assessors. The training visits are conducted by researchers who are not involved in outcome assessments.

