### Sample size and power calculation

Power calculations were performed with the software program G*Power 3.1.9.4 [74] and were based on the primary hypothesis that altitude-like hypoxia combined with cognitive training produces robust sustained cognitive improvement compared with normoxia and no training (hypothesis i). As hypoxia triggers the endogenous production of EPO, we based the power calculation on our previous clinical study of subcutaneous EPO treatment in which we demonstrated clinically relevant cognitive enhancement [75]. In that study, the differential change between EPO and placebo groups in the same cognitive composite score as we apply in the present study was 0.5 standard deviations (SD) [75]. Assuming an effect of 0.4 SD differential change (medium effect size) between the two groups and 0.5 SD of the change, we will achieve > 80% power to detect an effect at an alpha level of 0.05 by including 26 participants per group. This number of participants provides adequate power for the structural and functional MRI investigations based on our previous studies of EPO [30, 32, 33]. To accommodate for up to a 20% drop-out, we will include 30 participants per treatment arm; i.e., 120 participants in sub-study 1 and 60 patients in sub-study 2.

For PET imaging of SV2A [^11^C]UCB-J binding (reflecting presynaptic density), power calculations involved the following assumptions: (i) the average (SD) *BP*_ND_ in the frontal cortex in healthy participants is 3.36 (0.38) (based on in-house data), and (ii) the combined intervention will lead to a 10% increase in *BP*_ND_. With these assumptions, we will achieve a power of 0.82 to detect an effect at significance level of 0.05 post-treatment of the combined intervention (primary aim) with *n* = 20 per treatment arm using a two-tailed, independent-sample *t*-test.

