### Ethical considerations

A key ethical consideration is the extensive time requirement of participants over a period of three weeks. Given this, we will recruit primarily university students in the first study, since they are likely to have time. For patients with affective disorders, the extensive time requirement may be overwhelming. Therefore, we decided to give patients up to two days off (Saturday and Sunday) every week, (in contrast with only one day off for healthy participants, leading to a total of 16—as opposed to 18 in sub-study 1—treatment sessions over three weeks. We are monitoring patients’ mood state at continuous basis with daily brief monitoring of subjective state and any adverse reactions through the VAS and ESQ questionnaires and weekly mood ratings assessed with HDRS and YMRS, respectively. If patients show mood symptom exacerbation to a score of ≥ 18 on the HDRS or YMRS, they are followed up with one more rating after two days, and if no improvement is seen, they are referred to their psychiatrist and drop-out is considered. In our experience, patients with affective disorders generally find it meaningful to take part in cognition trials because of their intrinsic motivation to try new treatments that may reduce their debilitating cognitive difficulties. This has so far ensured high adherence to and satisfaction with study participation.

To minimize attrition and ensure motivation, we have chosen an online cognitive training program and matched computer games that are highly engaging, rewarding, and—for the active condition—neuroadaptive (for more details, see [52]). Finally, fMRI is non-invasive, and PET [^11^C]UCBJ will be associated with small exposure to radioactivity, not much more than the annual background radiation. PET [^11^C]UCBJ has been found safe in studies examining synaptic density in healthy adults [84], in adolescents [71] and in patients with Alzheimer’s disease [85] or depression [86].

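### The mean is the only summary named for the daily ESQ, and it does not show how many participants had altitude-sickness symptoms

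*Protocol article*

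**What the plan says.** Under Safety procedures and monitoring of hypoxia training, one of the listed precautions is to "monitor potential symptoms of altitude sickness at a daily basis with the Environmental Symptoms Questionnaire (ESQ) related to cerebral function". The same section gives the sponsor's judgement of the risk: "We therefore evaluate the risk of altitude sickness in our study as minimal". It closes with the reporting commitment: "We will report the mean ESQ scores in the primary outcome articles". That sentence goes on to promise a report of adverse events arising while participants are being treated.

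For patients, Ethical considerations describes "daily brief monitoring of subjective state and any adverse reactions through the VAS and ESQ questionnaires". Table 1 marks the ESQ in the active treatment phase for both sub-studies. It also schedules adverse-event assessment at baseline, during treatment, and at weeks 4 and 8.

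Randomization and blinding plans a check, after study completion, of whether each sub-study 1 participant stayed blind. The reason given is that "there is a small risk that some participants develop symptoms of mild altitude sickness which could unblind them to their intervention".

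No section gives an ESQ score that counts as a case, says that such a score is logged as an adverse event, or names a count or proportion of participants with symptoms.

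**The concern.** Altitude sickness happens to particular people on particular days, and the ESQ is taken daily in order to catch it. The natural summary is how many participants had it, and how badly. A mean answers a different question: the average symptom level. Brief illness in a few people can leave that average close to the level of a well group, and different patterns of illness can produce the same average.

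Two things are at stake. First, a low mean could be read as confirming the sponsor's view of the risk, whatever share of participants had symptoms. The Limitations section foresees later safety work in patients with somatic comorbidities, and for that a proportion affected is more useful than a mean. Second, in sub-study 1 the article itself links mild symptoms to loss of blinding. If those symptoms are not logged as adverse events, the mean is the only place where they appear, and it cannot be set against an individual's blinding result.

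**Working it through.** The article gives no ESQ range, standard deviation, cut-off or expected incidence, so there is no figure of its own to reproduce. The arithmetic below is illustrative.

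**Inputs from the article**
- Participants per arm: 30. Sample size and power calculation: "we will include 30 participants per treatment arm; i.e., 120 participants in sub-study 1 and 60 patients in sub-study 2".
- Sessions: 18 in sub-study 1 and 16 in sub-study 2. Ethical considerations: "leading to a total of 16—as opposed to 18 in sub-study 1—treatment sessions over three weeks".
- ESQ frequency: daily.

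**Assumptions**
- *k* participants score *s* points higher on *d* sessions, and everyone else is unchanged.
- The mean is pooled over all sessions. The article does not say whether it is pooled, per participant or per session.

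**Step 1: can the mean recover the number affected?**
Sub-study 1 has 30 × 18 = 540 records per arm. The shift in the pooled mean is *k* × *d* × *s* / 540.
- One participant ill on all 18 sessions: 1 × 18 × *s* / 540 = 0.033 *s*.
- Eighteen participants ill on one session each: 18 × 1 × *s* / 540 = 0.033 *s*.

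The mean is the same for 1 of 30 affected (3%) and 18 of 30 affected (60%). This needs no assumption about the ESQ scale.

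**Step 2: how small is the shift if pooled?** (*s* = 2 points, *d* = 2 sessions)
- 3 of 30 (10%): 3 × 2 × 2 / 540 = 0.022 points.
- 5 of 30 (17%): 5 × 2 × 2 / 540 = 0.037 points.

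**Step 3: how much depends on pooling?**
If the mean is given per session and the same cases fall on the same sessions, the shift on those sessions is *k* × *s* / 30.
- 3 of 30: 3 × 2 / 30 = 0.20 points.
- 5 of 30: 5 × 2 / 30 = 0.33 points.

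These are nine times the pooled figures. A per-session mean dilutes less, but it still does not count people: 3 participants 2 points higher and 6 participants 1 point higher both give 6/30 = 0.20.

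**Step 4: does stopping early lower the mean?**
Suppose the 3 cases stop after their 2 symptomatic sessions. Each loses 16 further records, 48 in all, and the shift becomes 12 / (540 − 48) = 12/492 = 0.024. That is slightly above 0.022. A downward pull requires the further assumption that those who stop would have stayed ill.

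**The case against.** The strongest reply is that the sentence does not end with the mean. It also commits the primary articles to reporting adverse events, and individual cases would be expected there. Adverse events are assessed throughout, the ESQ is described as a means of picking up adverse reactions, and Data management and monitoring records the reason for each withdrawal together with any adverse events. Blinding is checked directly for each participant. The article calls symptoms a small risk rather than an expected outcome. Finally, detailed tabulations are commonly left to the full protocol or the SAP, neither of which is shown.

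Much of this stands, and it rules out several stronger readings that a reader might infer:
- *That the mean is the only safety report.* The second half of the sentence contradicts this.
- *That the mean hides how many participants were unblinded.* The per-participant check addresses that directly, and patients in sub-study 2 are not blinded in any case.
- *That early stopping necessarily lowers the mean.* Step 4 shows a case where it does not.
- *That a 10 to 17% incidence would be invisible.* That depends on pooling, which the article does not state, and on a scale or standard deviation that it does not give.

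What the reply does not remove is the gap between the two reporting channels. The article has chosen a summary for the ESQ, and that summary does not count people. The adverse-event channel would fill the gap only if ESQ symptoms were turned into adverse events by a stated rule, and the article gives none. The blinding check shows whether blinding held, but not whether symptoms explain a failure.

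**Conclusion.** The point holds in a limited form. The mean is the only summary named for the daily ESQ, and it does not show how many participants had altitude-sickness symptoms. With no rule linking an ESQ score to an adverse event, mild symptoms of the kind that could unblind sub-study 1 participants may not be counted anywhere.

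Step 1 carries the conclusion: under pooling, 3% and 60% affected can give the same mean. The shifts of 0.022 to 0.037 points are an illustration only. They rest on assumed cases, scores and sessions and on pooling; a per-session mean could move by 0.20 to 0.33 points. The article does not misstate or contradict itself here. It names a summary poorly matched to the purpose of the measurement, and this is cheap to improve. The primary efficacy analysis is not affected.

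**What to change.** In Safety procedures and monitoring of hypoxia training, extend the reporting sentence so that the primary articles give, by arm:
- the number and proportion of participants reaching, on at least one session, an ESQ level pre-specified by the investigators;
- the distribution of each participant's peak ESQ score;
- the mean ESQ score by session number, as a supplement.

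State how ESQ scores feed adverse-event reporting, so that the two sources can be read together. In sub-study 1 only, tabulate the counts beside the blinding check already planned under Randomization and blinding. The choice of ESQ level belongs to the investigators and should be fixed before unblinded data are seen.

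The cost is a few lines of text and one short extra table from data already collected. No assessment is added and clinical management does not change.

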**Fig. 1 Fig1:**
[figure not shown]
Overview of events across parallel sub-studies

Sub-study 1 involves four intervention groups: (1) normobaric hypoxia (12% O_2_) combined with cognitive training, (2) hypoxia (12% O_2_) with no training, (3) cognitive training under normoxia (20% O_2_), and (4) normoxia (20%) with no training in a double-blinded controlled design. This design enables us to disentangle combined and separate effects of altitude-like hypoxia and cognitive training. Participants are randomized in blocks and undergo interventions in these groups for practical reasons. During the three-week treatment, participants breathe 12% ambient oxygen (≈ 4400 m altitude) or approximately normal sea-level oxygen (20%) in a treatment room, 3.5 h daily, six days per week (18 sessions in total). After a blood test (days 1, 6, 20) and light standardized breakfast, they enter the treatment room. Here, they sit at a desk separated by desk dividers. On iPads, they perform cognitive training or matched control games without cognitive benefits. Cognitive training is interleaved by short breaks, during which the participants can relax or walk on a treadmill inside the room. This is to avoid complete physical inactivity throughout the 3.5 h sessions and thereby make the sessions more pleasant for participants. Participants undergo cognition assessments in weeks 1 (baseline), 4, and 8 and functional and structural MRI in weeks 1 and 8, when red blood cell counts are comparable between groups. Participants in the two extreme groups (normobaric hypoxia with cognitive training and normoxia with no training) will also undergo PET scanning in week 4 (post-treatment). Participants will be recruited consecutively for the PET scans until an equal distribution in each of the extreme intervention arms (i.e., hypoxia with cognitive training and normoxia with no training), sex, and age group is achieved.

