Sub-study 2 involves two intervention groups: (1) normobaric hypoxia (12%) combined with cognitive training 3.5 h daily, five to six days per week for three weeks (16 sessions in total), and (2) treatment as usual (TAU) in an assessor-blind controlled design. Patients in the TAU group will initially be assessed at the same time points as the active group with neurocognitive testing at baseline, week 4, and week 8, fMRI at baseline and week 8, and PET in week 4. After completed testing at week 8, patients in the TAU group undergo the three-week active intervention, followed by one additional neurocognitive assessment and mood rating in the week after treatment completion. The inclusion of this TAU arm rather than an active control group was chosen to ensure patient motivation and minimize attrition in this time-intensive study. Similar study designs with TAU control groups are common in pro-cognitive intervention studies investigating novel treatments in mood disorders and schizophrenia [39, 40]. Although patients will not be blinded to their allocated treatment arm, neurocognitive test results are generally not susceptible to placebo effects [41, 42] and assessments will be carried out by blinded, fully trained research assistants (psychology students).

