### Outcome measures

For an overview of outcome assessment domains, measures, frequency, and timing, see Table 1. The outcome measures listed below are consistent with the latest recommendations from the International Society for Bipolar Disorders (ISBD) Task Force [54].

**Table 1 Tab1:** Schedule of enrolment, interventions, and assessments

**Timepoint**	**Pre-intervention**	**Baseline (week 0)**	**Active treatment phase**	**End of treatment (week 4)**	**Follow-up (week 8)**	**Additional end of treatment assessment (week 12)** For sub-study 2 TAU group

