**Intervention and safety outcomes**						
Repeated moderate hypoxia exposure or normoxia (3.5 h per day, five to six days per week for three weeks)			x			
Cognitive training or sham training (3.5 h per day, five to six days per week for three weeks)			x			
Blood sampling (blood counts)	x	x	x (days 1, 8, and 19)	x	x	
Safety monitoring and assessments of potential adverse events		x	x	x	x	/
Mood ratings (HDRS + YMRS)	x	x		x	x	/
ESQ			x			
VAS			x			

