**Other measures**						
DART		x				
CTQ	x					
SCIP	x					
Research biomarker blood samples			x (days 1 and 19)			

x = included in both sub-studies. / = included in sub-study 2 only

*Abbreviations*: *HDRS* Hamilton Depression Rating Scale, *YMRS* Young Mania Rating Scale, *ESQ* Environmental Symptoms Questionnaire, *VAS* visual analogue scale, *RAVLT* Rey Auditory Verbal Learning Test, *TMT-A* Trail Making Test Part A, *TMT-B* Trail Making Test Part B, *RBANS* Repeatable Battery for the Assessment of Neuropsychological Status, *WAIS-III LNS* Wechsler Adult Intelligence Scale version 3 Letter-number-sequencing, *RVP* Rapid Visual Information Processing (CANTAB, Cambridge Cognition Ltd.), *SWM* spatial working memory (CANTAB, Cambridge Cognition Ltd.), *OTS* One Touch Stockings of Cambridge (CANTAB, Cambridge Cognition Ltd.), *ERT* Emotion Recognition Task (CANTAB, Cambridge Cognition Ltd.), *SDMT* Symbol Digit Modalities Test, *WCST* Wisconsin Card Sorting Test, *Connor’s CPT* Connor’s Continuous Performance Test, *FAST* Functional Assessment Short Test, *CAVIR* Cognition Assessment in Virtual Reality test, *AQoL* Assessment of Quality of Life, *COBRA* Cognitive Complaints in Bipolar disorder Rating Assessment, *SDS* Sheehan Disability Scale, *WHOQOL-BREF* World Health Organization Quality Of Life, *WSAS* Work and Social Adjustment Scale, *PSQI* Pittsburgh Sleep Quality Index, *fMRI* functional magnetic resonance imaging, *PET* positron emission tomography, *DART* Danish Adult Reading Test, *CTQ* Childhood Trauma Questionnaire, *SCIP* Screen for Cognitive Impairment in Psychiatry (Danish version)

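### The adverse-event reporting sentence covers the intervention only, while Table 1 collects events to week 8 (week 12 for TAU), and the reporting period for TAU is left open

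*Protocol article*

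**What the plan says.** The section on safety procedures and monitoring of hypoxia training ends with the article's reporting commitment: the primary outcome articles will give mean ESQ scores "in addition to any adverse events that may occur during the intervention".

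Table 1 has a row headed "Safety monitoring and assessments of potential adverse events". It is marked at baseline, in the active treatment phase, at week 4 and at week 8 with the symbol for both sub-studies, and in the last column with the symbol for sub-study 2. The key reads "x = included in both sub-studies. / = included in sub-study 2 only". The last column is headed "Additional end of treatment assessment (week 12") and is labelled as applying to the sub-study 2 TAU group.

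The Methods give the length of treatment. In sub-study 1 it is three weeks with 18 sessions. In sub-study 2 it is "five to six days per week for three weeks (16 sessions in total"). TAU is listed there as one of two intervention groups and is assessed on the active arm's timetable to week 8. Then: "After completed testing at week 8, patients in the TAU group undergo the three-week active intervention", with one further assessment in the week after that course ends.

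**The concern.** The stated reporting scope is narrower than the trial's own collection schedule. If the authors follow the sentence as written, events that begin after the last session are recorded at the week 4 and week 8 visits but have no place in the primary safety report.

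In sub-study 2 there is a second difficulty. TAU patients receive no hypoxia or training before week 8 and the full active course afterwards. The phrase therefore does not settle which TAU events are reported. One reading gives a concurrent control rate. The other gives events under uncontrolled, delayed exposure, which could end up in the same table as the randomised data.

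For an intervention the authors themselves call novel, the reporting window should be fixed before results are seen, so that it is not chosen later between readings.

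**Working it through.** There is no stated figure to reproduce, and no power, rate or effect size enters. The check sets the passages side by side.

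**Collection against stated report**

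| Table 1 column | Adverse events assessed? | Within the three-week intervention? |
|---|---|---|
| Baseline (week 0) | Both sub-studies | No, before treatment |
| Active treatment phase | Both sub-studies | Yes |
| End of treatment (week 4) | Both sub-studies | No, visit falls after the last session |
| Follow-up (week 8) | Both sub-studies | No |
| Week 12 | Sub-study 2 TAU only | No, visit falls after the delayed course |

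The week 4 visit can still pick up events that began during treatment. What falls outside a literal reading is an event that first arises after the last session.

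**Length of the uncovered period**

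- If the three weeks run directly from week 0, treatment ends at about week 3, and 8 − 3 = 5 weeks remain to the week 8 visit.
- If treatment ends close to the week 4 visit, 8 − 4 = 4 weeks remain. This fits the Abstract, which calls the later visit a 1-month follow-up.

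The period is therefore roughly 4 to 5 weeks. This is calendar time between visits and says nothing about how many events to expect in it.

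**TAU in sub-study 2**

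- Reading A: TAU counts as an intervention group, so the phrase means the three weeks parallel to active treatment. Concurrent events are reported for both arms.
- Reading B: the intervention is the hypoxia training itself, so for TAU the phrase means the delayed course after week 8. Events from that course have no untreated group alongside them.

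The Methods support A by calling TAU an intervention group, and B by saying that TAU patients undergo the active intervention after week 8. No other sentence decides between them.

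**Sub-study 1**

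All four arms attend sessions over the same three weeks, so the TAU question does not arise for those 120 participants. It concerns the 60 patients of sub-study 2. The gap between the last session and week 8 concerns both sub-studies.

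**The case against.** The strongest reply is that this is a closing sentence in a paragraph on altitude sickness, worded as a positive promise. It does not say that later events will be left out. The article also undertakes to publish all results whatever their direction, and has adverse events documented at exclusion or withdrawal with no time limit. Event windows and the handling of crossover exposure usually sit in a full protocol or SAP, which is not shown.

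Much of this stands. A reader might infer that post-treatment events are deliberately excluded; the text does not say so. What remains is that the article does state a scope, and that scope does not match its own Table 1. That is different from being silent.

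Three further inferences are tempting and are not supported.

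- *That TAU has no comparison window.* It has one: adverse events are scheduled at baseline, week 4 and week 8 in parallel with the active arm. What is missing is a statement of which TAU period is reported. That delayed-course events lack a comparator follows from the design and not from the reporting sentence.
- *That the documents say blood counts still differ throughout the weeks after exposure.* The Methods place MRI in weeks 1 and 8, "when red blood cell counts are comparable between groups". This does not say when after treatment counts become comparable. Thromboembolic history is an exclusion criterion, but no post-exposure risk is described.
- *That a fixed share of adverse-event observation is lost, computed as post-treatment weeks over total weeks.* Table 1 lists assessment points and does not describe uniform continuous observation, so such a percentage has no basis in the documents.

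**Conclusion.** The point holds as a minor mismatch of reporting scope. The commitment covers three weeks of intervention; collection runs to week 8 for everyone and to week 12 for TAU after its delayed course. Taken literally, events first arising in the roughly 4 to 5 weeks before the week 8 visit are collected but not covered, and the TAU reporting period in sub-study 2 is ambiguous.

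This rests on a literal reading of the phrase and on the article alone; a full protocol or SAP may already state a wider window. No bias in the safety conclusion can be quantified from the documents, and none is claimed.

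**What to change.** Reword the reporting sentence in the safety section along these lines: all adverse events from baseline to week 8 will be reported by randomised arm over the same window, with TAU to week 8 as the concurrent control in sub-study 2, and split into on-treatment and post-treatment. Events in the TAU group from the start of the delayed course to the week 12 visit will be reported separately as uncontrolled data.

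The cost is one or two sentences. Table 1 already schedules the assessments, so nothing is added for participants.

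There is one small downside. Table 1 places the ESQ and VAS only in the active treatment phase, and the safety and ethics sections describe them as daily. This questioning appears to be tied to treatment sessions, which TAU patients do not attend before week 8. Ascertainment in sub-study 2 would then differ between arms, and this should be stated beside the table.
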